### *Methods for exploratory study*

Study arm: 2 arms study which consists of 15 healthy children in each arm with Fibersol-2 dosing 2.5 g twice daily and 5g twice daily respectively

1. Study group 1, 15 healthy children will receive Fibersol-2, 2.5g twice daily with 50 ml drinking water
2. Study group 2, 15 healthy children will receive Fibersol-2, 5g with 50 ml drinking water twice daily

Study arm: 2 arm study which consists of 15 diarrheal children in each arm with Fibersol-2 dosing 2.5 g twice daily and 5 g twice daily respectively

1. Study group 1, 15 diarrheal children will receive Fibersol-2, 2.5g twice daily with 50 ml drinking water
2. Study group 2, 15 diarrheal will receive Fibersol-2, 5g with 50 ml drinking water twice daily

### **Study duration:**

1. Pre-study observation: 7 days [During the pre-study observation period our study staff members will collect clinical information as well as associated co-morbidity from control group children to see whether they are eligible for enrolment].
  2. Main study period : 7 days
  3. Post-study observation: 7 days [Our research staff will visit households as well as hospital to collect 1-day recall data regarding health status; caregivers will be informed that the research staff will visit for consecutive 7 days]
- Total observation period 21 days

### **Study design for clinical efficacy trial**

The proposed clinical efficacy trial will be a placebo-controlled, randomized; double-blind 2 arm trial to assess the efficacy of low osmolarity ORS plus Fibersol-2 compared with low osmolarity ORS in the treatment of acute watery diarrhea in children.

### *Eligibility for assessing for clinical efficacy trial*

Eligible age for the study: 1-3 years

Genders eligible for the study: Both

Include only acute diarrheal children: Yes

### *Eligibility criteria for the clinical efficacy trial*

#### Inclusion criteria:

(i) Children with acute watery diarrhea, 3 or more watery stool in any 24-hour period of <7 days duration with none or some dehydration (ii) Aged between 1-3 years, and (iii) Received written consent from parents

#### Exclusion criteria:

(i) Children with bloody diarrhea, severe diseases (severe sepsis, meningitis, severe pneumonia with respiratory distress requiring intensive care and ancillary support such as oxygen inhalation, oropharyngeal suction etc.), (ii) Child in a situation and could interfere with the optimal participation to the study or constitute a particular risk of non-compliance, (iii) Currently participating in another clinical trial, and (iv) Parents refused to give written consent.

### *Methods for clinical efficacy trial*

A placebo-controlled, randomized; double-blind 2 arm trial to assess the efficacy of fibersol-2 in children with acute watery diarrhea. Children with acute watery diarrhea, 3 or more watery stool in any 24-hour period of <7 days duration with no dehydration.

Study group 1, 46 will receive Fibersol-2 dissolved in 50 ml drinking water, twice daily (suitable dose from the tolerability and acceptability trial)

Study group 2, 46 will receive Placebo (regular maltodextrin) dissolved in 50 ml drinking water twice daily (same dose as Fibersol-2)

An experienced researcher at icddr, b, not involved in the study, will prepare the randomization list using the randomization table. The name of random allocation will be indicated on a slip of paper, kept inside the sealed envelope. The sealed envelopes will be supplied to the researcher to supply the intervention package. The children with no dehydration or some dehydration will be randomized immediately after admission.

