#### **Case management**

Dehydration will be assessed according to the modified WHO guidelines followed in the hospital. In children with some dehydration, the fluid deficit will be corrected with ORS in an amount 10 ml/kg/hour for the first hours, then 5 ml/kg/hr until the deficit is corrected. In addition, ongoing stool losses will be replaced with ORS 5-10 ml/kg after each watery stool. For high purging children, the ORS intake will be adjusted according to the ongoing stool loss. ORS therapy will continue until diarrhoea stops. Mothers will be advised to continue breastfeeding.

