### **Sample Size Calculation and Outcome (Primary and Secondary) Variable(s)**

Clearly mention your assumptions. List the power and precision desired. Describe the optimal conditions to attain the sample size. Justify the sample size that is deemed sufficient to achieve the specific aims.

Based on the results of a clinical trial of ORS solution in children with acute watery diarrhea with an anticipation of a 25% reduction in 48-hour stool output after in children after receiving Fibersol-2 dissolved with drinking water. Considering 5% level of significance and 90% power and 10% drop out the sample size is estimated to be 46 in each group [14]. However, for the tolerability and acceptability study we have selected 30+30=60 children suggested by the respected members of the RRC and ERC respectively.

For the tolerability and acceptability study in healthy Study group 1, 15 healthy children will receive Fibersol-2, 2.5 mg twice daily

Study group 2, 15 healthy children will receive Fibersol-2, 5mg twice daily

For the tolerability and acceptability study in children with diarrhea Study group 1, 15 diarrheal children will receive Fibersol-2, 2.5g twice daily

Study group 2, 15 diarrheal children will receive Fibersol-2, 5g twice daily

For RCT in diarrheal children:

Study group 1, 46 will receive Fibersol-2 dissolved in 50 ml drinking water, twice daily (suitable dose from the tolerability and acceptability trial)

Study group 2, 46 will placebo (regular maltodextrin) dissolved in 50 ml drinking water, twice daily (same dose as in Fibersol-2)

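### The methods section limits the randomized trial to children with no dehydration, while the inclusion criterion and three other statements admit some dehydration; one criterion should appear throughout

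*Protocol*

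**What the plan says.** Five statements in the protocol bear on the dehydration status of children in the randomized trial.

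- **Eligibility criteria for the clinical efficacy trial, Inclusion criteria:** "Children with acute watery diarrhea, 3 or more watery stool in any 24-hour period of <7 days duration with none or some dehydration".
- **Methods for clinical efficacy trial, opening description:** "Children with acute watery diarrhea, 3 or more watery stool in any 24-hour period of <7 days duration with no dehydration".
- **Methods for clinical efficacy trial, closing sentence:** "The children with no dehydration or some dehydration will be randomized immediately after admission".
- **Introduction, final paragraph:** the same randomization sentence, repeated.
- **Case management:** "In children with some dehydration, the fluid deficit will be corrected with ORS", followed by the rehydration procedure.

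The Exclusion criteria begin "Children with bloody diarrhea, severe diseases (severe sepsis, meningitis, severe pneumonia with respiratory distress requiring intensive care" and go on to non-compliance risk, other trials and refusal of consent. Dehydration is not among them.

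The Baseline information section has the research physician assess and record dehydration. The Measurements section takes duration of diarrhea from randomization and names duration, recovery within 72 hours and daily stool output as primary outcomes.

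**The concern.** Who may be randomized is fixed by the protocol and cannot be left to an analysis plan. Here two sentences that share a case definition differ in the one phrase that decides whether a child with some dehydration can enter. Read by the methods description, enrolling that child is a deviation; read by the inclusion criterion, it is not. A monitor or ethics committee could not say from the text which enrolments complied.

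The choice also determines what the results describe. Children are randomized immediately after admission and duration is counted from randomization. If children with some dehydration are enrolled, correction of their fluid deficit falls inside the outcome period; children with no dehydration have no such phase. Daily stool output is a primary outcome, and the sample size rests on an "anticipation of a 25% reduction in 48-hour stool output". The two readings therefore give trials with different target populations for the same endpoints.

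**Working it through.** **Step 1. Set the statements side by side.**

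| Place in protocol | No dehydration | Some dehydration |
|---|---|---|
| Introduction, randomization sentence | admitted | admitted |
| Inclusion criteria | admitted | admitted |
| Methods, opening description | admitted | not admitted |
| Methods, closing sentence | admitted | admitted |
| Case management | – | provided for |
| Exclusion criteria | not mentioned | not mentioned |

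Of the five statements that speak to the matter, four admit or provide for some dehydration and one does not. The methods section conflicts with the inclusion criterion and also with its own last sentence. The body weight planned after rehydration, in the Measurements section, fits the majority reading.

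**Step 2. Can the effect on the sample size be computed?** The plan's figure is given as: "Considering 5% level of significance and 90% power and 10% drop out the sample size is estimated to be 46 in each group". No mean or SD of stool output is stated, so 46 cannot be reproduced forward. It can only be solved backwards for the coefficient of variation (CV = SD / control mean), assuming a two-sided test:

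- Evaluable per arm: 46 × 0.90 = 41.4, taken as 41.
- n = 2 (1.960 + 1.282)² CV² / 0.25², so CV = 0.25 / (3.242 × √(2/41)) = 0.35.
- Assumed CV 0.35: n = 42, and 42 / 0.90 = 46.7, so 47 per arm.
- Assumed CV 0.40: n = 54, and 54 / 0.90 = 60 per arm.

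The required number is sensitive to the spread of stool output, which is a reason to fix the population. But the protocol gives no stool output, mean or SD, by dehydration grade. Whether either reading would raise or lower the CV, and by how much, cannot be determined.

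**Step 3. Does the contradiction create imbalance between arms?** If a share p of enrolled children has some dehydration, the chance difference between arms in that share has, under unrestricted allocation (an assumption, since no scheme is named), SD = √(2p(1−p)/46):

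- p = 0.5: √(0.5/46) = 0.104, or 10.4 percentage points.
- p = 0.3: √(0.42/46) = 0.096.
- p = 0.2: √(0.32/46) = 0.083.

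The shares are assumptions; the protocol gives none. A 20-point difference at p = 0.5 is 20 / 10.4 = 1.9 SD. This is ordinary chance variation. It would be the same if every passage agreed on admitting both grades, so it does not measure the defect.

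**The case against.** The strongest reply is that the text has a clear majority reading. The formal criterion stands under its own heading, and the Baseline information section sends staff to the eligibility criteria. The outlying sentence is a verbless fragment in a methods paragraph that the same section contradicts. On this view it is a slip, and practice at the bedside would not turn on it. That largely stands, and it limits how serious the point is. It does not remove it: the fragment is current text in the section describing how the trial is run, and it states an eligibility limit.

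A reader might also infer more than the documents support:

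- **That dehydration grade is the dominant prognostic factor.** A link with stool output is plausible, but the protocol neither states nor quantifies one.
- **That inconsistent screening biases the comparison.** Eligibility is judged before allocation, which uses sealed envelopes in a double-blind design. Uneven screening could blur the target population or change the variance, but it would affect both arms alike.
- **That simple randomization will leave the arms unbalanced.** The protocol mentions only a randomization list and table and names no scheme. Chance imbalance is in any case allowed for by a valid randomized test.
- **That the trial is underpowered because of the wording.** Step 2 shows that this cannot be computed.

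**Conclusion.** The contradiction is established from the text alone and rests on no numerical assumption. One sentence excludes children with some dehydration and four statements include or provide for them. As written, the eligibility of such a child cannot be determined consistently, and the population to which the stool-output and duration results apply is not fixed.

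The size is modest. The formal inclusion criterion is clear in itself, the conflict comes from one sentence, and there is no demonstrable effect on sample size, power or bias. It is more than a background typo because it concerns who the trial enrols and to whom its conclusions apply. The calculations above rest on assumed CVs and shares; they show why the effect cannot be quantified and are not evidence of harm.

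**What to change.** The investigators should decide which population is intended and state one dehydration criterion in the Introduction, the Inclusion criteria, both sentences of the methods section, and Case management. Which grade or grades to admit is their decision. On the present text, the opening description in the methods section is the only statement out of line, so changing it would be the smallest edit. Either way the cost is a short amendment.

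If both grades are enrolled, two optional steps follow, and the point does not depend on them:

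- **Adjust the primary comparisons for baseline dehydration grade.** The assessment is already planned, so the only cost is recording the grade before randomization and naming the covariate in advance.
- **Or stratify the randomization list by grade, with blocking within each stratum.** Two unblocked lists would not balance the grades better than one list. The cost is a second envelope series and its handling.

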### **Statistical methods**

All data will be entered into microcomputer and analyzed using the software 'Statistical Package for Social Science'; version 20.0, Chicago, IL. Continuous variables will be compared between groups with student's t-test and nonparametric test. Categorical variables will be compared by chi-square test. Kaplan-Meier survival curves will be constructed for the duration of diarrhoea and for comparison with log rank test; a p value <0.05 will be considered as statistically significant. To see

whether there are significant differences among the groups, we will perform ANOVA to systematically examine variability within groups being compared.

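### The efficacy trial leaves its allocation type unstated and uses dehydration status, known before randomization, neither as a stratum nor as a covariate in the tests listed

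*Protocol*

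**What the plan says.** **Allocation.** Under Methods for clinical efficacy trial, and again at the end of the Introduction, the protocol says that a researcher outside the study "will prepare the randomization list using the randomization table". Concealment is by envelope: "The name of random allocation will be indicated on a slip of paper, kept inside the sealed envelope". No allocation type, block or stratum is named.

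**Arm sizes.** "Study group 1, 46 will receive Fibersol-2 dissolved in 50 ml drinking water, twice daily" and "Study group 2, 46 will receive Placebo (regular maltodextrin) dissolved in 50 ml drinking water twice daily". The sample size section repeats 46 per group.

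**Who is randomized.** The inclusion criteria admit acute watery diarrhoea "of <7 days duration with none or some dehydration". The allocation paragraph agrees: "The children with no dehydration or some dehydration will be randomized immediately after admission". Case management sets out rehydration for children with some dehydration. However, the opening paragraph of Methods for clinical efficacy trial describes the population as having diarrhoea "of <7 days duration with no dehydration".

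**Analysis.** "Continuous variables will be compared between groups with student's t-test and nonparametric test". Chi-square tests are listed for categorical variables, Kaplan-Meier curves with a log-rank test for duration, and ANOVA for differences among groups. No covariate or stratification factor is mentioned.

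**The concern.** Stool output and duration of diarrhoea may well depend on how ill the child is at entry. Dehydration status is one marker of that. Because eligibility turns on it, it is known before the envelope is opened. The plan collects it and then uses it nowhere: the allocation text does not balance it, and the listed tests do not adjust for it.

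With 46 children per arm, two things are at stake. One is precision: variation explained by dehydration stays in the error term. The other is credibility: if the arms differ visibly at entry, readers will not know how much of the observed difference to attribute to the product. A covariate can be added to the analysis later, but a stratified list has to exist before the first child is randomized.

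**Working it through.** **1. The trial's own sizing.** The inputs are a 25% reduction in 48-hour stool output, 5% significance, 90% power, 10% dropout and 46 per group. No mean or SD is given, so 46 cannot be reproduced directly. Working backwards, 41 evaluable per group gives 41/0.9 = 45.6, rounded up to 46. From n = 2 × (CV/0.25)² × (1.96 + 1.2816)², 41 per group implies a CV of 0.25 / (3.2416 × √(2/41)) = 0.349 two-sided, or about 0.39 one-sided. The two-sided value is used below.

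**2. Split, if the list is unrestricted 1:1 for 92 children.**
- P(exactly 46:46) = C(92,46)/2⁹² = 0.083.
- P(arms differ by 10 or more, such as 41:51) = 0.35; by 20 or more (36:56) = 0.047.
- Power, if 90% at 46:46, is 89.7% at 41:51 and 88.6% at 36:56. Averaged over all splits it is about 89.7%.

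**3. Chance imbalance in dehydration status at 46:46.** The share with some dehydration is not in the protocol; 20% to 50% is assumed. A gap of at least 15 points is a difference of 7 or more children (7/46 = 15.2 points).

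| Share with some dehydration | Each arm an independent binomial sample | Total in the trial held fixed |
|---|---|---|
| 20% | 0.089 | 0.064 |
| 30% | 0.139 | 0.112 |
| 50% | 0.175 | 0.144 |

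The first column is the one quoted in the conclusion; the second shows that the result depends somewhat on the model.

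**4. What such a gap does to mean output.** Let output with some dehydration be r times output with none, and let p be the share with some dehydration in an arm. The arm mean is proportional to 1 + p(r − 1). The ratio r is also an assumption.
- r = 1.5, arms at 57.5% and 42.5%: 1.2875/1.2125 = 1.062, a shift of about 6%.
- r = 1.25, same arms: 1.14375/1.10625 = 1.034, about 3%.

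For scale, the standard error implied by step 1 is 0.349 × √(2/41) = 0.077, or 7.7% of the mean. A 6% shift is about 0.8 of a standard error, so it lies within the uncertainty that the unadjusted test already allows for.

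**5. What adjustment would recover.** The share of variance due to status is p(1 − p)(r − 1)² / [1 + p(r − 1)]², divided by CV² = 0.349² = 0.122.
- r = 1.25, p = 0.2: 0.0091/0.122 = 7%.
- r = 1.5, p = 0.5: 0.0400/0.122 = 33%.
- r = 2, p = 0.5: 0.1111/0.122 = 91%. One baseline sign would then account for nearly all the variation the trial was sized on, which is not credible, so a two-fold ratio is not used.

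Removing 7% to 33% of the variance is worth 1/(1 − 0.07) = 1.08 to 1/(1 − 0.33) = 1.49 times the sample size for that comparison.

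**The case against.** The strongest reply is that most of this rests on silence. A list prepared in advance from a table can hold exactly 46 of each allocation. A reader might infer that randomization is simple and that 46:46 will rarely be achieved; the protocol does not say so, and the 8% figure holds only if the list is unrestricted. A reader might also picture staff closing an arm at 46 and sending the last children to the other. Nothing in the text describes that. Block sizes are often kept out of protocols on purpose. All of this stands, and with so little power at stake the missing allocation type alone is only missing detail.

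Second, it is tempting to say that chance imbalance biases the comparison. It does not: under valid randomization the unadjusted test keeps its 5% error rate. That also stands.

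Third, adjustment may sit in a statistical analysis plan that is not shown. This stands only in part. Such a plan could add a covariate to the tests the protocol names, but it could not create strata once enrolment has begun.

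Fourth, nothing in the protocol shows that dehydration is more prognostic than age, prior duration of diarrhoea or nutritional status. That is fair. The case for dehydration is that it is two-level, defines eligibility and is already assessed before allocation.

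Fifth, if only children without dehydration are enrolled, there is no stratum. That depends on reconciling the two eligibility statements.

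**Conclusion.** The concern holds as a missed gain in efficiency and robustness, not as a threat to validity. If both dehydration groups are enrolled, the plan ignores a baseline factor that it already has in hand. The chance of a gap of 15 points or more is about 9%, 14% and 17% at 20%, 30% and 50% prevalence. Such a gap at 50% prevalence would move mean output by about 6% if output differs 1.5-fold. Adjustment would remove about 7% to 33% of the variance for ratios of 1.25 to 1.5. Prevalence and ratio are assumptions, and the CV of about 0.35 is inferred from the stated sample size, not given. An unequal split, if it arises, costs about 0.3 points of power on average.

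**What to change.** 1. Reconcile the sentence in Methods for clinical efficacy trial that limits the population to no dehydration with the inclusion criterion that admits none or some. The remaining steps apply only if both groups are enrolled.
2. In the Introduction and in Methods for clinical efficacy trial, state that the list uses permuted blocks stratified by dehydration status at admission, with a separate envelope series for each stratum. Keep the block sizes in a restricted document, not in the protocol.
3. In Statistical methods, make the primary comparisons account for dehydration status: a linear model with treatment and status for stool output, a stratified log-rank test for duration, and a stratified test for recovery within 72 hours.

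The cost is a sentence in each of the two allocation passages, a revised analysis paragraph and a second envelope series prepared by the same independent researcher. There is slightly more handling at admission. Because blocks may be left incomplete in each stratum, the final arms may differ from 46:46 by a few children; with blocks of 4, for example, by at most 2 per stratum, so 4 overall.

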#### **Baseline information**

Children fulfilling the eligibility criteria will stay in the hospital throughout the study period until discharged. Research physician will take a detailed medical history of the enrolled children to determine the duration of and type of diarrhoea and its frequency; duration and frequency of vomiting; and presence of other symptoms such as fever, feeding difficulties, and treatment received for the illness before admission; and perform a thorough physical examination including assessment of dehydration according to the guidelines used in icddr,b and also the nutritional status will be measured and recorded.

#### **Case management**

Dehydration will be assessed according to the modified WHO guidelines followed in the hospital. In children with some dehydration, the fluid deficit will be corrected with ORS in an amount 10 ml/kg/hour for the first hours, then 5 ml/kg/hr until the deficit is corrected. In addition, ongoing stool losses will be replaced with ORS 5-10 ml/kg after each watery stool. For high purging children, the ORS intake will be adjusted according to the ongoing stool loss. ORS therapy will continue until diarrhoea stops. Mothers will be advised to continue breastfeeding.

